**Sample Size/Power Calculation**

Counts received from the GPRD show:

- ~2,000 registered patients have had bariatric surgery, with a mean follow up of 2.4 years
- ~80,000 patients have received a prescription for orlistat
- >1.4 million patients have a BMI >=30

QRESEARCH contains data on a similar number of patients to GPRD and we therefore anticipate the number of eligible patients for this study would be roughly double the numbers shown above.

Assuming we match 5 untreated patients to each patient with an obesity intervention, we would have 80% power to detect a reduction in mortality over 4 years amongst those undergoing surgery from 5% to 3.9% (over the whole 4 year period).

**Exposures**

Exposures will be defined as follows:

- First record of bariatric surgery with at least 12 months prior UTS registration
- A first prescription for orlistat with at least 12 months prior registration to ensure incident usage
- A first prescription for sibutramine with at least 12 months prior registration to ensure incident usage

**Outcomes**

Outcomes have been chosen as events that are well recorded by GPs as part of routine patient care, regardless of where a diagnosis is made (by the GP or in secondary/tertiary centres). Numerous studies have been published looking at these outcomes using data from the GPRD/QRESEARCH and validity has been shown to be high (GPRD, 2010; QRESEARCH, 2010). The following outcomes will therefore be ascertained for all patients in the cohort:

- Death
- Change in Weight
- Change in BMI
- Diabetes
  - First diagnosis
  - Progression to monotherapy with oral antidiabetic agent
  - Progression to polytherapy with oral antidiabetic agents
  - Progression to insulin therapy
  - Resolution (noted in GP record as patient removal from diabetes QOF register)
- Cardiovascular disease
  - Incident MI
  - Incident stroke
  - Onset of hypertension
  - Onset of angina
  - Improvement of hypertension determined by permanently stopping antihypertensive medication, i.e. at least 6 months without a further prescription
- Osteoporotic Fractures (hip, spine, wrist)
- Acute liver injury as indicated by a diagnostic code or a record of alanine transferase at >3X upper limit of normal in patients without chronic liver disease.
- Fatty liver
- Incident cancer diagnoses
- Obstructive sleep apnoea
- Change in lipid profile

In addition, within the GPRD, Hospital Episode Statistics (HES) data will be available for a large proportion of the cohort. We will therefore be able ascertain post-operative outcomes, including post-operative haemorrhage, post-operative infection, ITU admission, re-admission to hospital and re-operation. Also, within the GPRD, detailed information on acute coronary events will be available via linkages with the Myocardial Ischaemia National Audit Project (MINAP).

The research team has considerable experience in developing algorithms for determining outcomes based on both GPRD and is developing expertise with HES data – algorithms for specific outcomes are available on request.

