**Study Design and Study Population**

A combination of two UK databases offers an excellent opportunity to study the clinical effects of interventions for obesity; the UK General Practice Research Database (GPRD) and QRESEARCH. In combination the GPRD and QRESEARCH contain information from >1100 UK general practices, and have current and historical data for >20 million patients. Continuous patient records include details of all consultations, diagnoses, prescribed medicines and basic demographic data. Patients are representative of the England & Wales population in terms of age, sex and geographical distribution [refs]. Data quality is subject to rigorous checks and audits and >500 peer reviewed studies have been published using GPRD or QRESEARCH data including studies investigating unintended effects of medication (GPRD, 2010; QRESEARCH, 2010). GPRD and QRESEARCH draw information from mutually exclusive practices and are therefore fully complementary.

*3.1 Study Design - Patient population, exposures of interest, inclusion/exclusion criteria*

The cohorts will comprise obese patients registered in the GPRD and QRESEARCH:

- Eligible patients will be those aged 18+ years with at least 12 months research standard registration time in the GPRD or QRESEARCH AND with one of the following exposures recorded by the study start:
  - A record of bariatric surgery with at least 12 months prior registration to ensure incident status (specific type of bariatric surgery used will be determined using data recorded in patient records); OR
  - A first prescription for orlistat with at least 12 months prior registration to ensure incident usage; OR:
  - A record of BMI>30 with neither bariatric surgery nor a prescription for orlistat – these patients will act as the **comparison group**
- The date of surgery or first orlistat prescription will be termed the index date. Each patient with surgery or orlistat will be matched with up to 5 obese patients without a record of these treatments, on age (within 5 years), sex and practice with at least 12 months research standard registration prior to the relevant index date.
- Patients will be followed until the earliest of; an outcome of interest, death, transfer out of the practice or last data collection date.

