**Amendment 21 May 2015**

The following amendment is proposed

1. Health Survey for England estimates that currently 1.4 million residents in England are morbidly obese (BMI > 40kg/m2 ). For all outcomes where surgery appeared to have an effect, we will estimate the absolute number of outcomes that surgery could potentially prevent, by applying the relative risks obtained in our analysis to the rate of events detected in the non-surgery group, and scaling to 1.4 million people.
2. In order to maximise the study population size, we will no longer use MINAP and HES to ascertain MIs and will instead use first recorded MI in the CPRD GOLD record.

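### Cancer risk time starts at the index date with no latency period, so early diagnoses can bias the cancer hazard ratio in either direction

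*Protocol*

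**What the plan says.** The Outcomes section of the protocol lists "Incident cancer diagnoses" without further qualification. Section 3.1, under Study Design and Study Population, sets one time origin: "The date of surgery or first orlistat prescription will be termed the index date". Comparators are matched with reference to the treated patient's index date. Follow-up ends at the earliest of "an outcome of interest, death, transfer out of the practice or last data collection date". Neither these sections nor the later amendments delay the start of cancer risk time or exclude early diagnoses.

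Specific Aims promises a between-group comparison of cancer rates, but the Cox paragraph in Statistical Analysis and Covariates does not include cancer among the outcomes it names. The covariate list there does not mention cancer history, although the list is open-ended.

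Two later steps use apparent effects. Statistical Analysis and Covariates plans an NNT or NNH wherever a treatment effect is seen. Item 1 of the Amendment of 21 May 2015 scales results to 1.4 million people "For all outcomes where surgery appeared to have an effect".

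**The concern.** A cancer diagnosed soon after the index date may well have been present before it, and treatment can then have neither caused nor prevented it. Such cases do no harm to the comparison if they are equally frequent in both groups, but there are reasons to doubt that they are. A patient under investigation for possible cancer, or losing weight without explanation, may be less likely to go forward to surgery or to a weight-loss prescription. A comparator in the same state still enters follow-up on a date taken from someone else. Item 2 of the first Amendment adds to this asymmetry, because comparators for surgery qualify on a BMI of 40 or more recorded at any time while registered, not near the index date. In the other direction, investigation around surgery could bring forward diagnoses in the treated group.

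Propensity scores balance what is recorded, and an undiagnosed tumour is not recorded. Surgical follow-up is short on average, so the first year carries substantial weight. An artefact from that year could be reported as a cancer effect of surgery, turned into an NNT and scaled to a national count.

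**Working it through.** **Inputs from the protocol.** Mean surgical follow-up M = 2.4 years (Sample Size/Power Calculation: "2,000 registered patients have had bariatric surgery, with a mean follow up of 2.4 years"). The shape of follow-up is not given. The first Amendment, item 1, reports more than 3,000 surgery patients but no updated mean.

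**Assumptions.** Lag L of 12 months, with 6 and 24 months as a range. Follow-up exponential, uniform on 0 to 2M, or the same for everyone. M = 4 years as an alternative. First-year cancer rate ratio r, surgery against comparator, of 0.5 to 1.2. No true effect after year one.

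**The plan's own figures.** None is given for cancer. The only surgical power statement concerns mortality (80% for 5% against 3.9%). With about 4,000 surgery patients ("roughly double the numbers shown above") and five comparators each, two-sided 0.05 assumed, power comes to 86%. The 80% would need about 3,408 surgery patients. The statement is therefore conservative for that cohort and has no bearing on the cancer point.

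**Step 1: share f of person-time within L years of index.**

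- Exponential: f = 1 − exp(−L/M)
- Uniform: f = (L − L²/(4M))/M
- Fixed: f = L/M

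| M (years) | L (years) | Exponential | Uniform | Fixed |
|---|---|---|---|---|
| 2.4 | 0.5 | 0.188 | 0.197 | 0.208 |
| 2.4 | 1 | 0.341 | 0.373 | 0.417 |
| 2.4 | 2 | 0.565 | 0.660 | 0.833 |
| 4.0 | 1 | 0.221 | 0.234 | 0.250 |

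For example, 1 − exp(−1/2.4) = 0.341, (1 − 1/9.6)/2.4 = 0.373 and 1/2.4 = 0.417.

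**Step 2: apparent overall ratio with no true effect.** If the comparator cancer rate is constant over time and the ratio of treated to comparator patients at risk stays constant, the overall ratio is f·r + (1 − f).

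| r | f = 0.34 | f = 0.42 |
|---|---|---|
| 0.5 | 0.83 | 0.79 |
| 0.8 | 0.93 | 0.92 |
| 1.0 | 1.00 | 1.00 |
| 1.2 | 1.07 | 1.08 |

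With M = 4 (f = 0.22 to 0.25), r = 0.5 gives 0.89 to 0.88 and r = 1.2 gives 1.04 to 1.05.

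**Step 3: precision cost of a lag.** At a constant event rate the standard error of the log hazard ratio grows by 1/√(1 − f).

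- 12 months: 1/√0.659 = 1.23 to 1/√0.583 = 1.31
- 6 months: 1/√0.812 = 1.11 to 1/√0.792 = 1.12
- 24 months: 1/√0.435 = 1.52 to 1/√0.167 = 2.45

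**The case against.** The strongest reply is that this is an omission, not an error. Only the protocol is at hand, a cancer lag could sit in a separate analysis plan, and the Outcomes section says that outcome algorithms can be requested. Because cancer is missing from the Cox outcomes, one can also argue that no unlagged cancer analysis has been fixed. Part of this stands: a lag may exist elsewhere. But section 3.1 sets one time origin and one follow-up rule for the cohort, and anyone following it would count cancers from the first day. The protocol also sets time windows where it wants them, such as the 6 months without a prescription that defines improved hypertension and the 3-month extension after orlistat is stopped.

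A second reply concerns size, and it largely stands. The first-year ratios are assumed. The documents give no cancer rates and nothing on work-up before surgery. The 2.4-year mean describes the older count of about 2,000 patients. The route to the 1.4 million figure is also conditional. At an assumed 5 cancers per 1,000 person-years, 3,000 patients followed for 2.4 years yield 3,000 × 2.4 × 0.005 = 36 surgical events, with 180 among five times as many comparators. The standard error is then √(1/36 + 1/180) = 0.18, and a spurious ratio of 0.81 would have a 95% interval of about 0.57 to 1.16. Whether that would count as an apparent effect is unclear, because the amendment sets no criterion.

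A reader might infer that about a third of surgical follow-up reflects tumours already present at index. The documents do not support that: the 34–42% is a share of person-time in the first year, not of tumours or of biased cases, and it is a minority of follow-up. Nor do they support the inference that the plan will show a false cancer benefit. Equal early rates give no bias, and extra detection around surgery would give apparent harm.

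**Conclusion.** The point holds as a gap in how the cancer outcome is handled. As written, cancer risk time starts at the index date without latency, and the planned adjustment cannot correct for undiagnosed disease. On the stated 2.4-year mean and a 12-month window, 34–42% of surgical person-time is exposed to the problem, or 22–25% if the mean has risen to an assumed 4 years. With no true effect, the overall ratio would be about 0.79–0.93 for an assumed first-year ratio of 0.5–0.8, and about 1.07–1.08 for 1.2. These ranges rest on the assumed window, follow-up shapes and first-year ratios, and on a constant comparator rate. That a bias can arise follows from the plan; its presence, direction and size cannot be determined from the documents. The remedy is a cheap improvement that should be made. Whether a lagged estimate should replace the unlagged one as the main result is debatable.

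**What to change.** In Outcomes and in Statistical Analysis and Covariates:

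1. Add cancer to the outcomes analysed by Cox regression.
2. Exclude from the cancer analysis any patient with a cancer record before risk time starts, in treated and comparator groups alike.
3. Pre-specify a lagged cancer analysis, for example with risk time starting 12 months after the index date, and show 6 and 24 months. Apply the lag identically to treated patients and their matched comparators, and report the result beside the unlagged estimate.
4. State that a cancer NNT or NNH, and the scaling in item 1 of the Amendment of 21 May 2015, will be given for cancer only if the lagged estimate supports the effect.

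This needs wording and a few extra model runs, with no new data. The cost is precision in the lagged estimate: with 12 months it loses about a third or somewhat more of surgical person-time (34–42%), and its standard error is about 23–31% wider. The 24-month version is much less precise (standard error 1.5 to 2.4 times as large) and serves only as a check on direction. The lagged estimate also applies only to patients still alive, cancer-free and under follow-up when the lag ends, which the report should say.

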**Statistical Analysis and Covariates**

*Baseline Comparisons*

We will use baseline data to compare the background characteristics of patients receiving surgical and pharmacological interventions for obesity with those receiving no intervention. This will give a broad picture of how these interventions are being targeted in the UK as a whole. Odds ratios and 95% confidence intervals will allow us to determine statistically and clinically relevant differences, using patients with no intervention as the baseline group. As a subgroup analysis, differences in the targeting of specific forms of bariatric surgery will also be determined. **Covariates** to be assessed will include age, sex, weight, BMI, smoking status, alcohol consumption and a range of co-morbidities such as coronary heart disease, hypertension and diabetes.

*Cohort analysis*

We will compare outcomes between patients receiving surgical and pharmacological interventions for obesity with those receiving no intervention. It is anticipated that these three groups of patients will differ in fundamental ways related to health outcomes that could represent important bias and confounding in this study. For this reason we will calculate propensity scores for each patient, capturing their likelihood to receive either surgery or a prescribed anti-obesity therapy. Using the propensity scores we will ensure comparisons are only made between patients with similar background characteristics (Sturmer et al, 2010). Cox proportional hazard regression will be used to conduct time to event analyses for death, diabetes, cardiovascular disease, fractures and liver disease, adjusting for the propensity score. Patients with no intervention will form the baseline group.

In addition, anonymised, linked Hospital Episode Statistic (HES) data are available for patients in the GPRD and will allow us to look in detail at hospital records for patients who undergo bariatric surgery (e.g. type of surgery, any complication that arise).

Patients who receive orlistat and later have surgery will move from one exposure group to the other, according to current treatment. We anticipate that very few patients will receive orlistat following surgery and any patients who appear to do so will be excluded from the analysis.

For exposure to orlistat, follow up time will be censored 3 months after the date when prescribing information indicates treatment was stopped. This period allows for a degree of medication stockpiling and a treatment washout period. Similarly, follow up time for controls matched to orlistat recipients will be censored at the same date ensuring similar follow up in comparison groups.

Sensitivity analyses will stratify orlistat exposure on dose and duration using recorded prescribing information to estimate daily dose and duration of treatment.

Where possible, we will calculate number needed to treat (NNT) or number needed to harm (NNH) for clinical outcomes where a treatment effect is seen.

Linear regression will be used to compare changes in weight and BMI between surgical or pharmacological interventions and no intervention, adjusting for the propensity score. Changes will be calculated annually.

Similarly, a paired t-test will be used within each treatment group to determine changes in weight and BMI from baseline (pre-intervention). Changes will be calculated annually.

Absolute rates will also be determined for post-operative complications (post-operative haemorrhage, post-operative infection, ITU admission, re-admission to hospital and re-operation). Cox regression will be used to compare the hazard for each event between different types of bariatric surgery.

Initially the analysis will be done separately for QRESEARCH and GPRD data. It is anticipated the results will be very similar since the two datasets represent different samples of the same underlying population. Assuming the results are similar, data will be pooled, and a single analysis will be done, which will increase precision.

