**Amendment**

A number of amendments to this protocol are now sought:

1. Due to funding constraints, it will not be possible to access QRESEARCH data and the study will be restricted to CPRD data only. We do not anticipate major changes to the feasibility of the study, as the current number of patients in the CPRD with bariatric surgery is now >3,000.
2. Following initial data processing it became apparent that matches for bariatric surgery patients, drawn from the population of patients with a BMI >30 were very dissimilar from the surgery patients, mainly because the surgery group tended to have a much higher BMI. Since the guidelines for surgery include a requirement of BMI >=40 in most instances, we propose matches to be drawn from a pool of patients with any measure of BMI >=40 during their registration.
3. For the analysis of weight loss, we intend to measure the effects to a maximum of three years post-intervention, largely driven by the amount of follow up available for surgery patients
4. Following statistical advice from [name], it was decided that mixed effects linear regression should be used to assess changes in weight and BMI over time within each group. We anticipate a non-uniform rate of change over follow up and will model this using splines. The Akaike Information Criterion (AIC) will be used to determine optimal spline knot points. From the final model, weight/BMI and 95% confidence intervals for the study population will be estimated. The rate of change in weight or BMI and 95% confidence intervals will be calculated for each spline component.
5. For all other outcomes, orlistat patients will be censored at the end of follow up, analogous to an intention to treat type analysis, so the long term consequences of the decision to start a course of treatment with orlistat can be measured, regardless of subsequent treatment. As a sensitivity analysis, follow up will be censored at the estimated date treatment was stopped, based on prescribing records.
6. Subgroup analyses according to underlying diabetes and cardiovascular disease status will be carried out, in line with NICE recommendations for research on treatments for obesity. Additionally, where numbers permit, analyses of bariatric surgery patients will be stratified by surgery type.
7. As a clarification, patients who have bariatric surgery and later receive orlistat will be excluded from orlistat analyses only.

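### The protocol specifies no estimate of early death after surgery: death is missing from the planned absolute post-operative rates, and the only model stated for it gives one overall hazard ratio

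*Protocol*

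**What the plan says.** Death is an outcome for every patient (Protocol, Outcomes), and mortality rates are to be compared between groups (Specific Aims). The model is in Statistical Analysis and Covariates: "Cox proportional hazard regression will be used to conduct time to event analyses for death, diabetes, cardiovascular disease, fractures and liver disease", adjusted for the propensity score, with untreated patients as reference. On timing, Study Design and Study Population says: "The date of surgery or first orlistat prescription will be termed the index date". Follow-up from that date is implied rather than stated.

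For early harm, Statistical Analysis and Covariates says: "Absolute rates will also be determined for post-operative complications (post-operative haemorrhage, post-operative infection, ITU admission, re-admission to hospital and re-operation". The bracket closes after re-operation, so death is not in it.

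Two other absolute measures could reach death. One is the number needed to treat or harm, calculated where a treatment effect is seen. The other is the scaling to 1.4 million people in the Amendment of 21 May 2015, for outcomes where surgery appeared to have an effect. Neither has an early window.

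On follow-up, Sample Size/Power Calculation reports about 2,000 "registered patients have had bariatric surgery, with a mean follow up of 2.4 years". Amendment item 1 later says that "the current number of patients in the CPRD with bariatric surgery is now >3,000". Item 3 caps the weight analysis at three years, "largely driven by the amount of follow up available for surgery patients".

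**The concern.** An operation carries risk in the first weeks, and any survival benefit comes later. A proportional-hazards model reports one average of the two periods, and the weight given to the early one depends on how long patients are followed.

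The Lay Summary says that the results should help doctors and patients choose between treatments, and the risk of dying soon after the operation bears directly on that choice. The protocol decides which post-operative events get absolute rates, and the gravest one is not named. Background & Rationale notes that the earlier English study of short-term mortality had no non-surgical comparison. This study has that comparison but does not specify the early result.

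If early harm and later benefit happened to offset each other, the number needed to treat and the scaling to 1.4 million might not be calculated for death at all, since both depend on an effect being seen.

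**Working it through.** **1. The plan's own mortality figure.** Sample Size/Power Calculation claims "80% power to detect a reduction in mortality over 4 years amongst those undergoing surgery from 5% to 3.9"%. On a constant-hazard scale this is a hazard ratio (HR) of ln(0.961)/ln(0.95) = 0.776. With 5:1 matching and an assumed two-sided 5% level, 80% power needs 3,408 surgery patients by a two-proportion calculation, or about 3,030 by Schoenfeld's formula. The roughly 4,000 patients implied by doubling the first database's count give 86% or 90%. The plan does not state the number behind its 80%, and this point does not depend on it.

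**2. Untreated risk.** From 5% over 4 years, the hazard is −ln(0.95)/4 = 0.01282 per year. The 30-day risk is 1 − exp(−0.01282 × 30/365.25) = 0.105%, and the 90-day risk is 0.315%.

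**3. Assumptions not in the protocol.** 30-day surgical mortality p of 0.1% to 1.0%, and HR 0.70 after day 30. The scenario has 3,000 surgery patients (Amendment item 1), 15,000 untreated (5:1) and 2.4 years of follow-up. The 2.4 years belongs to the earlier count of about 2,000 patients; the mean for the later cohort is not given.

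**4. Formulas.**
- Early HR = −ln(1 − p)/(0.01282 × 30/365.25).
- Overall HR: the single value that solves the expected Cox score equation under this two-period hazard.
- Standard error of log HR = √(1/d1 + 1/d0), where d1 and d0 are surgical and untreated deaths.
- Untreated deaths are 454.6 in all, 15.8 within 30 days and 438.8 after. Surgical deaths are 3,000p early and about 61.5 later.

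| Assumed 30-day risk | Early surgical deaths | 30-day HR (95% CI) | Overall HR (95% CI) |
|---|---|---|---|
| 0.1% | 3 | 0.95 (0.3 to 3.3) | 0.71 (0.55 to 0.92) |
| 0.2% | 6 | 1.9 (0.7 to 4.9) | 0.74 (0.57 to 0.96) |
| 0.3% | 9 | 2.9 (1.3 to 6.5) | 0.775 (0.60 to 1.00) |
| 0.5% | 15 | 4.8 (2.4 to 9.6) | 0.84 (0.66 to 1.07) |
| 1.0% | 30 | 9.5 (5.2 to 17.6) | 1.01 (0.80 to 1.26) |

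The HR after day 30 is 0.70 (0.54 to 0.91) in every row. The intervals ignore matching and propensity-score restriction.

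**5. Dependence on follow-up.** For follow-up of 1, 2.4 and 4 years, the overall HR is 0.72, 0.71 and 0.71 at p = 0.1%, and 1.04, 0.84 and 0.79 at p = 0.5%. Staggered follow-up averaging 2.4 years also gives 0.84 at p = 0.5%.

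**6. The converse.** Hold 4-year mortality at the plan's 3.9% against 5% and vary only the early share. For p of 0.1%, 0.3%, 0.5% and 1.0%, the later HR is 0.77, 0.73, 0.69 and 0.59, while the overall HR stays between 0.776 and 0.779. The overall HR tracks net mortality, but here it does not show when the deaths occur.

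**7. Choice of cut.** If the excess is confined to 30 days, the 90-day surgical risk is 1 − (1 − p)exp(−0.70 × 0.01282 × 60/365.25), which is 0.447% at p = 0.3% and 0.647% at p = 0.5%. The 90-day HRs are then 1.4 (0.8 to 2.6) and 2.1 (1.2 to 3.5), against 2.9 and 4.8 at 30 days.

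**The case against.** The best reply has four parts.

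**Analysis-plan content.** Proportional-hazards checks and period splits commonly sit in a statistical analysis plan, and that plan is not shown. This stands for the split, which is therefore offered only as a supportive analysis. The list of absolute post-operative rates is protocol text.

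**The list does not exclude death.** Outcomes introduces the same five events as examples, and hospital data are to be used to examine any complication. This also stands. A reader might infer that early deaths are ignored, or that the protocol rules out reporting them. The text does not support either: early deaths enter the Cox model, and the gap is that no early estimate is specified. Nor is the overall hazard ratio wrong. With equal follow-up it lies within 0.01 of the cumulative mortality ratio in these scenarios.

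**Scope.** The objective is long-term outcomes, and short-term mortality had been studied in about 7,000 English patients. This lowers the priority. It does not remove the point, because early deaths are part of the long-term hazard ratio and that study had no untreated comparison.

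**Undocumented inputs.** The early risk and the later HR of 0.70 are assumptions, and 2.4 years comes from an older count. This stands, so the size can only be given as a range.

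**Conclusion.** The point holds as a cheap improvement of optional to moderate priority. The protocol specifies no estimate of early surgical mortality: the absolute post-operative rates leave death out, and the one model stated for death in surgery versus untreated patients gives a single hazard ratio.

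That hazard ratio is a fair summary of net mortality over the follow-up observed, but it depends on follow-up length if risk is early and benefit late. How much is unknown. Under the stated assumptions the effect is negligible at a 30-day risk of 0.1% and material from about 0.3% to 0.5%. At 0.5% the overall result reads as no clear difference, while the early and later hazard ratios point in opposite directions. A reader might conclude that the mortality analysis is invalid or that a true benefit will be masked. The protocol does not support that, because it gives no surgical 30-day risk and the masking appears only in part of an assumed range.

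**What to change.** In Statistical Analysis and Covariates:

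- Add all-cause death within 30 and 90 days of surgery to the post-operative outcomes, as absolute risks with 95% confidence intervals.
- Keep the overall surgery-versus-untreated Cox hazard ratio. Beside it, as a supportive analysis, report the hazard ratios before and after a cut fixed in advance at 30 days, since a 90-day cut dilutes an excess confined to the first month.
- Check operation dates, and deaths in operated patients, against Hospital Episode Statistics in the linked subset. Limitations warns that surgery paid for abroad may reach the GP record late or never, so GP records alone could understate early mortality.
- Give early deaths by surgery type only under the condition already in Amendment item 6: "where numbers permit, analyses of bariatric surgery patients will be stratified by surgery type".

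The cost is one tabulation, one extra pair of hazard ratios from an existing model, and the check in the linked subset. The downside is few events: about 3 to 15 early deaths per 3,000 at 0.1% to 0.5%, and fewer after propensity-score restriction. The early hazard ratio will be imprecise; at 0.2% its interval includes 1. The absolute risk is still useful: 9 deaths in 3,000 gives an exact interval of 0.14% to 0.57%, and 15 gives 0.28% to 0.82%.
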